## Abstract

**Background:**

Most women with breast cancer experience a progressive weight gain during and after treatment. Obesity is associated with an increased risk of recurrence, contralateral breast cancer, and death. Physical activity after cancer diagnosis has been reported to have positive effects on body composition and quality of life. We present the protocol of the InForma study, a trial testing the efficacy of an intervention on weight loss (≥5 % of the baseline body weight) in a group of overweight or obese breast cancer survivors.

**Methods/design:**

This is a four-arm randomized controlled trial. Patients will receive a 6-month intervention and be followed for a further 18 months. Intervention is designed to improve adherence to a healthy diet and/or to increase physical activity, taking advantage of a wrist-based activity monitor. Participants will be recruited among overweight or obese breast cancer patients treated at the European Institute of Oncology, after completion of eventual adjuvant chemotherapy and/or radiotherapy. It is envisaged that 260 patients will be randomized into four arms: Dietary Intervention; Physical Activity Intervention; Physical Activity and Dietary Intervention; and Less Intensive Intervention. Women will be offered individualized counseling consisting of face-to face discussion and phone calls in addition to group meetings. A motivational interviewing approach will be used to encourage health behavior change. All participants will be given a pedometer device to monitor their physical activity. Participants’ dietary intake will be repeatedly assessed using a validated food frequency questionnaire. Participants’ quality of life and anxiety will be assessed with the Functional Assessment of Cancer Therapy-Breast and the State-Trait Anxiety Inventory questionnaires. Blood samples will be collected at baseline and follow-up visits to assess lipid and hormone profiles. Body composition will be repeatedly assessed using bioelectrical impedance vector analysis for identifying changes of fat and fat-free mass. Women allocated to the less intensive intervention arm will be considered as the control group.

**Discussion:**

While there is a rising concern about the role of obesity in cancer recurrence and survival, this trial with its multi-arm design, motivational approach and use of a pedometer device will provide important insights regarding the most effective approach in promoting weight control in breast cancer survivors.

**Trial registration:**

ISRCTN53325751 (registration date: 16 October 2015); ClinicalTrials.gov NCT02622711 (registration date: 2 December 2015).

## Background

Breast cancer is the most frequently diagnosed form of cancer and the leading cause of cancer death among women worldwide, with an estimated 1.7 million new cases and 521,900 deaths in 2012 [1]. According to the association of Italian Cancer Registries [2], breast cancer is also the most common cancer in women in Italy with 581,373 newly diagnosed cases in 2010. The estimated incidence is stable and mortality is decreasing mainly due to advances in diagnosis and treatment. Consequently survival from breast cancer has improved, and currently about 87 % of breast cancer patients in Italy survive more than 5 years [2].

Modifiable lifestyle factors such as obesity, physical inactivity and excessive alcohol consumption are established risk factors for the development of, and death from, breast cancer [3, 4]. There is also accepted evidence that, after a diagnosis of breast cancer, being overweight or obese is associated with an increased risk of breast cancer relapse, death [5, 6], or second primary contralateral breast cancer [7–9]. In a recent meta-analysis including more than 200,000 patients with breast cancer, Chan et al. [10] demonstrated a 41 % increase in overall mortality in obese and 7 % in overweight women and a 35 % increase in breast cancer-specific mortality in obese women and 11 % in overweight women, as compared with patients who had normal weight at diagnosis.

Most women experience a progressive weight gain during and after treatment for breast cancer [11, 12] due to the changes in hormone levels and body composition associated with treatment. Weight gain usually ranges from 2–6 kg in the first year following diagnosis, but greater gains are also common [13]. Chemotherapy is associated with weight gain due to a reduced metabolism and the subsequent induction of menopause increasing the likelihood of weight gain [13]. Moreover treatment-related side effects, duration of treatments and psychological distress may affect diet and physical activity patterns compromising energy balance in ways that promote weight gain.

High body mass index (BMI) results in an increased production of hormones (estrogens, insulin, leptin), and pro-inflammatory cytokines, which have, in turn, been associated with breast cancer risk [14, 15]. In fact, estrogenic stimulation promotes breast cancer pathogenesis and tumorgenesis, while insulin and leptin exhibit proliferative, mitogenic, and anti-apoptotic activities in mammary cells, thus promoting tumor growth [16]. High circulating estrogen levels are associated with increased risk of breast cancer recurrence [17, 18].

Alongside this, physical inactivity represents a leading cause of death worldwide [19]. Regular physical activity yields a wide range of health benefits, because it is associated with healthier levels of circulating hormones (insulin, leptin and insulin-like growth factor (IGF)-1 and IGF-3, estrogens and androgens) [20, 21] as well as possibly strengthening the immune system [22]. Moreover physical activity after breast cancer diagnosis has also been reported to have positive effects on body composition, psychological outcomes, and quality of life (QoL) [23].

The number of trials of weight loss interventions in breast cancer is increasing, but a demonstration of their benefit on breast cancer outcome is limited [24]. Weight loss resulting from intentional increased physical activity and caloric restriction can improve hormonal status, quality of life, and physical functioning among obese and overweight breast cancer survivors [9, 24, 25]. Regular physical activity and healthy dietary habits are important factors for reducing the risk of cancer recurrence and mortality, as well as lifestyle-related chronic conditions [7, 26]. Few intervention trials in breast cancer survivors, integrating physical activity and dietary intervention have been initiated or conducted so far [24, 27, 28].

Despite the accumulating evidence of the detrimental effect of physical inactivity and being overweight on breast cancer risk and risk of breast cancer recurrence, weight control and physical activity counseling are not yet current practice. Clinicians typically try to advise patients to change their lifestyle habits using a directing style but this approach is often ineffective. Patients often seem ambivalent or unmotivated in respect to these messages and, in turn, generate resistance or passivity. Motivational interviewing is an alternative approach to discussing behavior change that fosters a constructive specialist-patient relationship and leads to better outcomes for patients. This intervention, aimed at encouraging positive health behavior changes within a medical setting, is promising [29], and it can help individuals to enhance adherence to diet and exercise modification programs [30].

The prognostic role of body mass index has been previously assessed on the outcome of a consecutive series of women treated at our institution (the European Institute of Oncology (IEO), Milan, Italy) for an aggressive form [estrogen receptor/human epidermal growth factor receptor 2 (ER-/HER2)-positive] of breast cancer. In these patients, obesity was significantly associated with the risk of developing distant metastases and with worse overall survival [31].

Given the above considerations, our aim is to evaluate the effect of a 6-month intervention on weight loss in a group of overweight or obese women treated for early breast cancer. The intervention is designed to improve adherence to a healthy diet or/and to increase physical activity and decreased sedentary time, taking advantage of a wrist-based activity monitor (pedometer device).

## Methods/design

### Study design

The present study (InForma) was designed as a mono-institutional randomized controlled four-arm parallel-group trial. Randomized patients will receive a 6-month intervention and will be followed for further 18 months (Fig. 1).

**Fig. 1 Fig1:**
[figure not shown]
Study flowchart

### Study population and randomization

Potential study participants will be recruited among all overweight or obese breast cancer patients treated at the IEO after breast cancer treatments (surgery, chemotherapy and/or radiation therapy) have been completed. Women undergoing hormone therapy will be eligible for the study. Groups of eligible participants will be invited at IEO for further eligibility assessment and enrolment. On arrival, they will receive a progressive number from the front desk receptionist. After an information meeting, they will be invited to sign all the study documents (informed consent form, privacy disclosure). Height, weight, waist and hip circumferences, and body composition will be measured. Participants who are eligible will receive the study questionnaires to be filled in. They will then be called following their random arrival number and be allocated in a 1:1:1:1 ratio to one of the four intervention arms: Dietary Intervention (DI); Physical Activity Intervention (PAI); Physical Activity and Dietary Intervention (PADI); or Less Intensive Intervention (LII) following a pre-established randomization list (Fig. 1). The randomization list was created using a computer random number generator and securely kept by a study collaborator not involved at the front desk. Randomization is not stratified, but blocks of 20 were created to achieve balance in the allocation of participants to the four treatment arms. The randomization list is not known to the front desk receptionist (administrative staff) who provides the progressive number that will be matched with the randomization number at the end of the information meeting. Randomization will be made by a member of the InForma study team (dietician or physiotherapist). This to ensure that allocation cannot be guessed before registration. Allocation is fixed and cannot be changed after randomization.

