The intervention will begin with an intensive phase consisting of monthly contacts: three face-to-face meetings, one group meeting and two motivational phone calls. The group sessions are planned for closed groups of an average of ten women per arm and will consist of a motivation and information session to discuss strategies and to reinforce guidance. The participants may invite a caregiver or a relative during the group meeting. The meeting aims to offer a caring and supportive environment where its members support each other and explore new strategies to create long-lasting positive changes. At baseline, their requirement for weight maintenance will be calculated using the Schofield equation [32] and then multiplied by their current physical activity level before applying a caloric restriction of about 500–1000 kilocalorie (kcal)/day [33, 34].

Individualized goals will be set for all participants included in the three intervention arms to promote weight loss. These goals will be verified at each contact and workable solutions will be proposed in case of specific problems. The contents of all contacts are presented in Table 2.

**Table 2 Tab2:** Delivery and contents of the 6-month intervention visits for participants randomized to the intervention arms: Dietary Intervention (DI); Physical Activity Intervention (PAI); Physical Activity; and Dietary Intervention (PADI)

	Contact 1	Contact 2	Contact 3	Contact 4	Contact 5	Contact 6
Contact	Face-to-face	Telephone	Group meeting	Face-to-face	Telephone	Face-to-face
Time line	1 month (following baseline assessment)	2 months	3 months	4 months	5 months	6 months
Duration	30 min	15 min	90 min	30 min	15 min	30 min
Who delivers	Dietician and/or physiotherapist	Dietician and/or physiotherapist	Psychologist, dietician and physiotherapist	Dietician and/or physiotherapist	Dietician and/or physiotherapist	Dietician and/or physiotherapist
Social support	-	-	Invited friend/partner/family member	-	-	-
Motivational approaches	1/2 week diet/activity diaries assessment	Identify perceived diet/activity challenges	Coping and provide opportunities to learn from each other	1/2 week diet/activity diaries assessment	Identify perceived diet/activity challenges	1/2 week diet/activity diaries assessment

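### The described randomization procedure does not secure its claim that allocation cannot be guessed: list places may be matched before consent, and list access is ruled out only for the receptionist

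*Protocol article*

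**What the plan says.** All of this is in the Protocol article, mostly under Study population and randomization.

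- **Invitation.** "Groups of eligible participants will be invited at IEO for further eligibility assessment and enrolment". Eligibility is therefore not fully settled when the women come.
- **Number.** "On arrival, they will receive a progressive number from the front desk receptionist".
- **Consent.** "After an information meeting, they will be invited to sign all the study documents (informed consent form, privacy disclosure"). Measurements follow, and women found eligible are given the questionnaires.
- **Allocation.** "They will then be called following their random arrival number and be allocated in a 1:1:1:1 ratio" from a list prepared in advance. "Randomization is not stratified, but blocks of 20 were created to achieve balance".
- **Matching.** A later sentence says the progressive number is matched with the randomization number when the information meeting ends.
- **Who knows the list.** A study collaborator with no front-desk role keeps it securely. The receptionist is said not to know it. Nobody else is mentioned.
- **Who randomizes.** "Randomization will be made by a member of the InForma study team (dietician or physiotherapist").
- **The claim.** The next sentence reads "This to ensure that allocation cannot be guessed before registration".

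Under Intervention, the baseline assessment is placed before randomization. In Table 2 the delivery row gives "Dietician and/or physiotherapist" for five of the six contacts. The third contact, the group meeting, adds a psychologist.

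**The concern.** Concealment requires that nobody who can influence whether a woman enters knows, or can work out, the arm she would get. The safeguard stated here covers the receptionist, who hands out numbers and is given no stated part in consent or eligibility. It does not cover the people who do the randomizing, and they hold the same job titles as those who deliver the arms. The timing is also unclear: one sentence links the woman to the list before she has consented or been measured.

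If an upcoming arm were known, the judgement of who is able to take part, or the way consent is discussed, could shift even without intent. Motivation and fitness bear directly on 6-month weight, the primary outcome. Selection of that kind at entry cannot be reliably repaired in the analysis.

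**Working it through.** The article gives no figure for concealment, so the main check sets its statements side by side.

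**1. Sequence.** In the order given under Study population and randomization:
1. number handed out on arrival;
2. information meeting;
3. consent;
4. measurements;
5. questionnaires to the women found eligible;
6. call by arrival number, and allocation.

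The matching sentence puts the link to the list at the end of step 2. The allocation sentence puts it at step 6, and the Intervention section agrees with step 6. The two timings differ by consent, measurement and the eligibility decision.

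**2. What the arrival number fixes.** The article does not say what happens to the number of a woman who declines or is found ineligible. There are two readings.
- *One-to-one matching.* Her list place is fixed on arrival, before consent. If she does not go on, the place is lost. The planned list is 260 / 20 = 13 blocks, with 20 / 4 = 5 women per arm in each. One lost place leaves 20 − 1 = 19 women in a block, which cannot split 5:5:5:5. With d lost places, the 13 blocks yield 260 − d women.
- *The list moves up.* Only her order in the queue is fixed, and the blocks stay intact.

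**3. Who could know the next arm.** The receptionist is excluded. The list-keeper's only stated restriction is having no front-desk role. For the dietician and physiotherapist nothing is stated.

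**4. How much the block size alone could reveal.** Assume that staff know the block size is 20 and keep a full tally of past allocations. The article states neither.
- Expected number of assignments that are certain, if each allocation is known before the next woman is decided on: 4 × 5 / (20 − 5 + 1) = 20 / 16 = 1.25 per block, and 1.25 / 20 = 6.25 %.
- Best-guess success on the same condition, by simulating permuted blocks: about 41 %, against 1 / 4 = 25 % by chance.
- Women are invited in groups, and allocation seems to follow once the group's paperwork is done. If only earlier sessions' allocations are known when a session's eligibility is settled, the simulation (20,000 blocks, sessions aligned to blocks, session size assumed because it is not given) yields:

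| Women per session | Best guess correct | Certain |
|---|---|---|
| 1 | 41 % | 6 % |
| 4 | 36 % | about 0.1 % |
| 5 | 35 % | below 0.01 % |
| 10 | 31 % | 0 % |
| 20 | 25 % | 0 % |

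- For comparison, with allocations known one at a time, smaller blocks are easier to guess: about 52 % for blocks of 4, 47 % for 8 and 44 % for 12.

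Block size is thus a minor leak. Possible access to the list itself matters more, because whoever sees the list knows every coming arm.

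**The case against.** The strongest reply is that the article is a condensed account. The list is computer-generated and securely kept by someone away from the front desk, and who sees it and how places are released may be set out in the full protocol. Table 2 lists roles, not individuals, and the article does not say who judges eligibility or takes the measurements. With any list prepared in advance the next arm already exists before consent, so what counts is who knows it. Under the reading in which the list moves up, the arrival number is already just a queue number.

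Most of this stands, and it limits the point to a weakness. It does not remove the point, because the article does more than leave detail out: it describes a mechanism, gives two timings for it, and states that it ensures concealment.

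Three stronger readings are tempting and are not supported:
- **That staff could manipulate the calling order.** Women are called by a number issued by a receptionist who does not know the list, so the randomizing staff do not choose who takes the next place. That is a real protection.
- **That staff can foresee 6 % of assignments and guess 41 % correctly.** This holds only if each allocation is known before the next woman's eligibility is decided and staff know the block size.
- **That each woman's arm is fixed before consent.** This holds only under one-to-one matching, which the article neither states nor rules out.

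**Conclusion.** The point holds in limited form. As written, the procedure does not secure the concealment it claims, for two reasons: the time at which the arrival number is matched to the list conflicts with the later allocation step and with baseline assessment before randomization, and access to the list is excluded only for the receptionist while the randomizing falls to the roles that deliver the intervention. Nothing in the article shows that an allocation was known in advance or that entry was influenced.

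The possible bias in the weight comparison cannot be sized from the document. The part that can be sized, guessing from the block pattern, runs from 25 % (chance) for assumed sessions of 20 women up to about 41 % for one woman at a time, given the assumptions in the check. A reader might infer that the list must be regenerated with varying block sizes. The figures do not support that: a block of 20 is already harder to guess than blocks of 4, 8 or 12. The loss of block balance is conditional on one-to-one matching. The change is worth making because recruitment is reported as ongoing and the remedy is cheap.

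**What to change.** For the women still to be enrolled:
1. Use the arrival number for queueing only.
2. Once consent, eligibility and baseline measurements are recorded, have the existing list-keeper release the next unused allocation by phone or by sequential sealed opaque envelope. The list-keeper should not deliver the intervention.
3. State that dieticians and physiotherapists cannot see the list or coming allocations.
4. Reconcile the sentence on matching at the end of the meeting with the later allocation step. Releasing the next unused allocation also settles what happens to the place of a woman who declines or is ineligible: it passes to the next woman and the blocks stay whole.

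The cost is a procedural note, a call or an envelope per woman, and a few minutes' delay each. If the current list-keeper delivers the intervention, custody must pass to someone who does not. The list, sample size and analysis stay as they are.

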### Study outcomes

The main aim of the study is to evaluate the impact of a 6-month intervention program on body weight change (weight loss ≥5 % of the baseline body weight) in overweight or obese breast cancer survivors.

As secondary outcomes, we will further examine the impact of the intervention on long-term weight control or maintenance, physical activity and inactivity levels, dietary intake, health status, and quality of life. We will also examine the effect of intervention on blood lipid profile [total, high-density lipoprotein (HDL), low-density lipoprotein (LDL) and very low density lipoprotein (VLDL) cholesterol and triglycerides] and on estradiol, C-reactive protein (CRP), insulin, and glucose at 6-, 12- and 24-month visits.

### Inclusion criteria

The study will be open to overweight or obese (BMI > 25 kg/m2) women, aged 18 years or older, who have been treated for a histologically confirmed, invasive, non-metastatic breast cancer and have completed their main cancer treatment (surgery, chemotherapy, radiation therapy) for more than 6 months.

Only those women who are able to participate in the intervention, who agree to wear the wrist-based activity monitor during the study period, and who sign the informed consent form and the privacy disclosure, will be enrolled.

### Exclusion criteria

Women satisfying any of the following criteria will not be eligible for the study: previous severe medical condition(s); advanced age impeding their adherence to the planned study schedules; contraindications to exercise due to any heart condition, stroke, chest pain during activity or rest; severe hypertension and any orthopedic complications that would prevent optimal participation in the physical activities prescribed; unable to walk for exercise (self-reported); symptoms of alcohol or substance dependence.

Other non-medical exclusion criteria are: lack of transportation to the study location over the study period; plans to move away from Lombardy or to be inaccessible for more than 3 weeks during the intervention period.

### Intervention

The principal aim of the intervention is to promote weight loss through diet and physical activity alone or in combination. The target goal is a 5 % weight loss 6 months after randomization. Participants will be followed up for a further 18 months and secondary outcome assessments will be made at 12 and 24 months (Table 1).

**Table 1 Tab1:** Study assessments

Assessments	Instrument	Visits			
		Baseline	6-month	12-month	24-month
Total, HDL, LDL and VLDL cholesterol, triglycerides, estradiol, insulin, glucose and C-reactive protein	Blood test	√	√		√
Height^a^, weight, waist and hip circumference, body mass index, waist-to-hip ratio	Calibrated scales, stadiometer, tape measure	√	√	√	√
Body composition (including total body water (TBW), body cell mass (BCM), extracellular water (ECW), fat-free mass (FFM), fat mass (FM) and percentage fat mass (% FM)	Bioelectrical impedance vector analysis (BIVA) (Nutrilab device, AKERN Srl – Italy)	√	√	√	√
Dietary target	24 hr recalls and/or food diary	√^b^	√		
Steps	Pedometer-like device	√^b^	√		
Diet	Food Frequency Questionnaire (FFQ)	√	√		√
Quality of life	Functional Assessment of Cancer Therapy- Breast (FACT-B)	√	√		√
Mood	State-Trait Anxiety Inventory (STAI)	√	√		√
Physical activity	International Physical Activity Questionnaire (IPAQ)	√	√		√

^a^Height will be assessed only at baseline

^b^24 hr recalls and/or food diary and the pedometer-like device will be used during the intervention to monitor individualized goals

Baseline assessment will be made for all participating women, prior to randomization in one of the four intervention arms (DI, PAI, PADI, and LII). All participants must wear the wrist-based activity monitor during the 6-month intervention period (day and night).

Participants randomized to one of the three intervention arms (DI, PAI, and PADI) will be given individualized counseling based on their lifestyle habits to reduce their weight. The motivational interviewing approach will be used to discuss behavior change that fosters a constructive specialist-patient relationship which could lead to better body weight control for the patients.

The intervention will begin with an intensive phase consisting of monthly contacts: three face-to-face meetings, one group meeting and two motivational phone calls. The group sessions are planned for closed groups of an average of ten women per arm and will consist of a motivation and information session to discuss strategies and to reinforce guidance. The participants may invite a caregiver or a relative during the group meeting. The meeting aims to offer a caring and supportive environment where its members support each other and explore new strategies to create long-lasting positive changes. At baseline, their requirement for weight maintenance will be calculated using the Schofield equation [32] and then multiplied by their current physical activity level before applying a caloric restriction of about 500–1000 kilocalorie (kcal)/day [33, 34].

Individualized goals will be set for all participants included in the three intervention arms to promote weight loss. These goals will be verified at each contact and workable solutions will be proposed in case of specific problems. The contents of all contacts are presented in Table 2.

**Table 2 Tab2:** Delivery and contents of the 6-month intervention visits for participants randomized to the intervention arms: Dietary Intervention (DI); Physical Activity Intervention (PAI); Physical Activity; and Dietary Intervention (PADI)

	Contact 1	Contact 2	Contact 3	Contact 4	Contact 5	Contact 6
Contact	Face-to-face	Telephone	Group meeting	Face-to-face	Telephone	Face-to-face
Time line	1 month (following baseline assessment)	2 months	3 months	4 months	5 months	6 months
Duration	30 min	15 min	90 min	30 min	15 min	30 min
Who delivers	Dietician and/or physiotherapist	Dietician and/or physiotherapist	Psychologist, dietician and physiotherapist	Dietician and/or physiotherapist	Dietician and/or physiotherapist	Dietician and/or physiotherapist
Social support	-	-	Invited friend/partner/family member	-	-	-
Motivational approaches	1/2 week diet/activity diaries assessment	Identify perceived diet/activity challenges	Coping and provide opportunities to learn from each other	1/2 week diet/activity diaries assessment	Identify perceived diet/activity challenges	1/2 week diet/activity diaries assessment
	Identify perceived diet/activity challenges	Provide feedback and encouragement	Review and discuss members’ goal evaluations	Identify perceived diet/activity challenges	Provide feedback and encouragement	Identify perceived diet/activity challenges
	Identify motivations, confidence, ambivalence regarding lifestyle change	Revaluate motivations, confidence, ambivalence regarding lifestyle change	Evaluate and discuss members’ motivation to change	Provide feedback and encouragement Revaluate motivations, confidence, ambivalence regarding lifestyle change	Revaluate motivations, confidence, ambivalence regarding life style change	Provide feedback and encouragement Revaluate motivations, confidence, ambivalence regarding lifestyle change
Informing change	Healthy eating and activity principles Portion size	Discuss experience of changing diet and activity referring back to perceived challenges at previous visit.	Provide general advice for psychological well-being and health promotion	Discuss experience of changing diet and activity referring back to perceived challenges at previous visit.	Discuss experience of changing diet and activity referring back to perceived challenges at previous visit.	Discuss experience of changing diet and activity referring back to perceived challenges at previous visit.
	Energy-dense food and drinks Activity and inactivity	Check for queries or areas of confusion or elaboration		Check for queries or areas of confusion or elaboration	Check for queries or areas of confusion or elaboration	Check for queries or areas of confusion or elaboration
	Discuss pedometer data	Discuss pedometer data		Discuss pedometer data	Discuss pedometer data	Discuss pedometer data
Personal goals	Setting diet or activity personal goals	Discuss self-monitoring of personal goals	-	Discuss self-monitoring of personal goals	Discuss self-monitoring of personal goals	Discuss self-monitoring of personal goals
		Provide positive feedback		Provide positive feedback	Provide positive feedback	Provide positive feedback
		Identify new personal goals or redefine old ones		Identify new personal goals or redefine old ones	Identify new personal goals or redefine old ones	Negotiate key long-term diet and activity goals based on: perceived achievements
						Summarize success
	Identify next appointment	Confirm group meeting	Identify date for next appointment	Identify date for motivation call	Identify last appointment	Identify date for motivation call

From 6 months onward, participants will be monitored by phone calls during which the strategies and guidance discussed in the face-to-face sessions will be repeated and reinforced.

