### LII arm

Participants included in the LII arm will be considered as the control group. They will receive general counseling on health to reduce weight, and be provided with materials and guidelines available to the general public [4, 34, 35] and receive two motivational phone calls.

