### Statistical methods

All continuous variables (anthropometric, biomedical, nutritional and psychological measurements) at baseline and at the primary time point (6-month) will be checked for normality and transformed as needed. The Student *t* test, analysis of covariance (ANCOVA) and multiple linear regression models will be used to assess changes in means before and after the intervention. All tests will be two-sided and *P* values <0.05 will be considered statistically significant.

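### Three of the four arms meet in closed groups of about ten, but neither the named analyses nor the sample size allows for correlation within those groups

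*Protocol article*

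**What the plan says.** Women are randomized individually: the Study population and randomization section has them "be allocated in a 1:1:1:1 ratio to one of the four intervention arms", in blocks of 20.

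Under Intervention, the six monthly contacts in DI, PAI and PADI are "three face-to-face meetings, one group meeting and two motivational phone calls". The group sessions are for "closed groups of an average of ten women per arm", in a setting where "its members support each other and explore new strategies to create long-lasting positive changes". Table 2 puts the session at month 3, gives it 90 minutes, and is headed as applying to the three intervention arms only.

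The LII arm section lists general counseling and public materials, and says that women "receive two motivational phone calls". No group meeting is listed for them.

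Statistical methods names the Student t test and says that "analysis of covariance (ANCOVA) and multiple linear regression models will be used to assess changes in means before and after the intervention", two-sided at 0.05. Sample size uses a two-sample t test with 65 women per arm, SD 9 kg and a difference of 3.75 kg. Neither section mentions group membership, an ICC or a design effect. Trial status reports that recruitment is ongoing.

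**The concern.** A closed group whose members are meant to influence each other is a plausible source of correlated outcomes. One group may gel and lose more weight than average, another less. If so, 65 women in six or seven groups carry less information about the arm mean than 65 independent women do. LII has no such structure, so the extra variance sits on one side of each comparison with control.

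A test that ignores this uses too small a standard error. Confidence intervals would be too narrow and the nominal 5 % level would not be held. Narrow intervals remain a problem when the intervention works, because an intervention that works can work unevenly across groups. A comparison of two intervention arms, which the Discussion's interest in the most effective approach invites, would carry the extra variance on both sides.

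**Working it through.** **Inputs from the article.** Group size m = 10 (Intervention). 65 women per arm, SD 9 kg, difference 3.75 kg, two-sided alpha 0.05 (Sample size). Groups per arm: 65/10 = 6.5, so six or seven.

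**Assumed.** The ICC is not given. The range 0.01 to 0.05 is used, with 0 as reference, on whatever scale is analysed.

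**The plan's own power figure, without grouping.** Standard error = 9 × √(2/65) = 1.579 kg. 3.75/1.579 = 2.375, and 2.375 − 1.960 = 0.415, so power = Φ(0.415) = 66 %. The stated 80 % is not reproduced and would need 91 women per arm. This is a separate and larger problem. It matters here because there is no spare power to absorb any grouping.

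**Allowing for grouping.**
- Design effect in an intervention arm: DE = 1 + (m − 1) × ICC = 1 + 9 × ICC.
- LII women are independent, so the variance of a difference against LII is inflated by (1 + DE)/2, and true SE / naive SE = √((1 + DE)/2).
- Actual type I error against LII = 2 × [1 − Φ(1.96 / SE ratio)].
- Between two intervention arms the SE ratio is √DE.
- Power with grouping allowed for = Φ(3.75 / (9 × √((1 + DE)/65)) − 1.96).

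| ICC | DE | SE ratio v LII | Type I error v LII | Type I error, two intervention arms | Power v LII, 65 per arm |
|---|---|---|---|---|---|
| 0 | 1.00 | 1.000 | 0.0500 | 0.0500 | 66 % |
| 0.01 | 1.09 | 1.022 | 0.0552 | 0.0605 | 64 % |
| 0.02 | 1.18 | 1.044 | 0.0605 | 0.0712 | 62 % |
| 0.05 | 1.45 | 1.107 | 0.0766 | 0.1036 | 57 % |

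The naive standard error against LII is too small by 1 − 1/1.022 = 2 % at ICC 0.01 and by 1 − 1/1.107 = 10 % at ICC 0.05.

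**Check by simulation.** The plain t test on 65 independent LII women against 65 women in six groups of ten and one of five (100,000 runs) rejected a true null in 4.9, 5.4, 6.1 and 7.5 % of runs at ICC 0, 0.01, 0.02 and 0.05. This agrees with the formula.

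**What the ICC means in kilograms.** On raw 6-month weight with SD 9 kg, ICC 0.05 implies a group-to-group SD of √0.05 × 9 = 2.0 kg, and ICC 0.01 implies 0.9 kg. After baseline adjustment far less is needed. With an assumed correlation of 0.9 between baseline and 6-month weight, the residual variance is 81 × (1 − 0.81) = 15.4 kg². A group SD of 0.5 kg then gives ICC 0.25/15.64 = 0.016, and 0.9 kg gives 0.81/16.2 = 0.05.

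**The case against.** A reader might infer that the standard errors are certainly too small and that the type I error certainly exceeds 5 %. The article does not support that. Both statements need an ICC above 0, and none is given.

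The other side has further points:

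- *The group contact is limited.* It is one contact in six, goals are set individually, and Table 2 shows no goal-setting or pedometer review at the group session. This stands as a reason to expect a small ICC. It is not a reason to expect zero: the session is 90 of 210 scheduled minutes (43 %), and mutual influence is its stated purpose.
- *Strict null.* Groups form after individual randomization, so if the intervention affects no one the meeting creates no correlation. This stands. The type I error figures therefore apply when group effects vary around a zero mean. The point does not protect intervals when the intervention works, or comparisons between active arms.
- *High ICCs look implausible.* On raw weight, 0.05 implies a group SD over half the planned 3.75 kg effect. This stands for the unadjusted t test, but much less so for a baseline-adjusted analysis, as shown above.
- *The powered comparison is each arm against LII.* This stands. No head-to-head test is specified, so the 6 to 10 % figures are secondary.
- *An unseen full protocol or SAP may deal with it.* It may: the regression models named do not exclude a group term. The sample size here has no allowance, however, and no later model can use a group identifier that was not recorded.

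A reader might also add clustering by shared counsellors. Nothing in the article ties a counsellor to a closed group, and LII women also receive motivational calls, so that argument is not relied on here.

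**Conclusion.** The point holds in conditional form. Three arms are partly delivered in closed groups and the control arm is not, and neither the stated analyses nor the sample size allows for it. If the within-group ICC is 0.01 to 0.05, standard errors against LII are understated by about 2 to 10 %, and the type I error of the nominal 5 % test is about 5.5 to 7.7 % when group effects vary around zero. Comparisons of two intervention arms, if made, would be at about 6 to 10 %. If the ICC is zero, the planned analysis is sound on this point.

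The figures rest on the assumed ICC range, on groups of about ten, and on an analysis that treats women as independent. This is a cheap improvement to the plan, and it ranks below the power discrepancy in Sample size.

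**What to change.** Record in the database the closed group to which each woman in DI, PAI and PADI belongs, starting now while recruitment continues.

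Analyse 6-month weight with the baseline-adjusted model plus a random intercept for group in the intervention arms only. Enter LII women as singletons and use Satterthwaite or Kenward-Roger degrees of freedom. If the plain ANCOVA is kept as the main analysis, pre-specify this model as a sensitivity analysis. Report the estimated ICC either way.

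The cost is one database field and one model term. Intervals will be slightly wider, and the group variance will be estimated imprecisely from six or seven groups per arm. If it is estimated as zero, the result is essentially the planned ANCOVA.
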